### Blinding

Both participants and the research team involved in the trial will be blinded about the groups. The groups will be observed in an identical manner by the study team to ensure randomization. Further, to ensure that the study team is double-blinded, the potential participant receiving the intervention or usual care will be contacted by a research assistant outside the research team. The 2 groups will be followed up for 26 weeks to determine whether there are any differences in outcomes between them. The results and subsequent analysis of the trial will be used to assess the effectiveness of the WTC portal, which is the extent to which the service benefits the patients rather than doing them any harm.

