## Methods

### Trial Design

The Let’s Act on Mental Health study is a longitudinal, fully remote, equally randomized (1:1), double-blind, alternative intervention–controlled, parallel-group randomized controlled trial to be conducted between October 2023 and April 2024 with a prospective follow-up for 26 weeks. This trial will evaluate whether digital interventions such as WTC improve population mental health trajectories over time. The trial will consist of 1 baseline assessment at week 0, 13 biweekly short and long follow-ups from week 24, intervention monitoring twice at weeks 6 and 26, and 1 final assessment at the end of the 26-week follow-up period. An overview of the trial process is shown in Figure 1.

The study’s overall objective is to evaluate the effectiveness and cost-effectiveness of the WTC portal by conducting a randomized controlled trial. We will use a “Knowledge-to-Action Framework” [14] with extensive stakeholder and cross-sectoral engagement and will incorporate program elements with people with lived experience.

The research questions we seek to answer with this study are the following: (1) how effective is the WTC portal in altering the trajectories of mental health and substance use, primarily anxiety, compared to usual care? (2) What is the benefit of WTC versus usual care in terms of incremental costs, health outcomes, ongoing recruitment, and maintenance costs compared to the cost per quality-adjusted life year (QALY) gained using these interventions? (3) What is the differential impact of WTC by age, sex or gender, race, and socioeconomic status?

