### Randomization

At week 1, after baseline assessments, participants will be randomly allocated through email invitation to intervention or control groups using a simple randomization method equivalent of tossing a coin to ensure double-blinding. Participants deemed eligible after a manual-fraud check will be emailed a personalized URL invitation based on the groups in the study by the research personnel within the study, using the email template attached.

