### Intervention

The intervention group will be invited to the WTC portal, which provides options for digital interventions. A single-sign on system used by WTC will be used to facilitate ease of transfer.

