### Control

The control group will be referred to the usual care tools available on the CAMH website, particularly (different mental health programs and resources such as “Game Changers: Self-care information,” which is a hub of resources to help start conversations about health, self-help booklet series, relaxation guides, and free web-based education with a personalized dashboard), which provides an opportunity to clients for self-monitoring (symptoms or physiological processes), build awareness, improve self-efficacy, and visualization. The control group will not receive process monitoring assessments at week 6 or 26. Service usage and contamination in the control group will not be monitored.

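### The trial is labelled double-blind, but the arms are sent to two differently named services with no masking described, and the sections disagree on who sends the group-specific invitations

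*Protocol article*

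**What the plan says.** The Abstract and the Trial Design section both give the label; Trial Design describes the study as "fully remote, equally randomized (1:1), double-blind". The Blinding section spells out the claim: "Both participants and the research team involved in the trial will be blinded about the groups". It adds that both groups will be observed identically.

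The arms receive different services. In the Intervention section, "The intervention group will be invited to the WTC portal, which provides options for digital interventions", with entry through WTC's single sign-on. In the Control section, "The control group will be referred to the usual care tools available on the CAMH website".

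The means offered for blinding participants is in the Randomization section, which allocates "using a simple randomization method equivalent of tossing a coin to ensure double-blinding". For the study team, the sections give two accounts of who contacts participants about their group:

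- Randomization: eligible participants "will be emailed a personalized URL invitation based on the groups in the study by the research personnel within the study".
- Blinding: the participant "will be contacted by a research assistant outside the research team".

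Table 1 lists the GAD-7 among the self-reported questionnaires. The Statistical Analysis section makes change in anxiety the primary trajectory and expects the effect to appear in self-reported mood.

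**The concern.** A double-blind label tells readers that knowledge of the arm cannot have shaped participants' behaviour, their answers or the way staff followed them up. If participants can see which service they were given and also score the outcome, expectation can influence the comparison and the label hides it. If in-study staff know the allocation, effort spent on reminders and on people drifting out of follow-up could also differ by arm. The Limitations section mentions self-report only for WTC usage, not for the outcome, so the article does not warn of either route.

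**Working it through.** No figure in the article is at issue, so the check compares its sections.

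**1. Can participants be blinded to group?** The two services have different names and different sites, and one has its own sign-on. A participant who follows the invitation sees which service was received. The article describes no sham, common front end or neutral name. What could still be masked is the hypothesis, or which service is the one under test. That is less than being blinded about the groups, which is what the Blinding section claims.

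**2. Does simple randomization supply blinding?** No. It makes the next assignment unpredictable, but it does nothing to hide the arm once the invitation arrives. In the same way, observing groups identically, which the Blinding section offers as ensuring randomization, bears on equal treatment and not on how people were allocated.

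**3. Who assesses the outcome?** The participant does, through self-reported questionnaires that include the GAD-7. The outcome is therefore not assessed by anyone blinded to the service received.

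**4. Who sends the group-specific invitation?** Randomization says personnel within the study; Blinding says an assistant outside the research team. Ethical Considerations also has research staff emailing a personalized link, but that link leads to the baseline questionnaire before allocation, so it does not settle the conflict. On a plain reading of Randomization, the in-study senders know the allocation.

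**5. Are the groups observed identically?** The sections disagree:

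| Section | Monitoring at weeks 6 and 26 |
|---|---|
| Blinding | both groups observed identically |
| Control | no process monitoring of the control group |
| Limitations | control-group usage and contamination not evaluated |
| Duration and Assessments | both groups' assessments described as including process monitoring |
| Table 1 | monitoring listed for WTC and usual care |

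If Control is right, the survey schedule itself could show the arm to anyone handling it.

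**6. What is the scale?** From Sample Size: 1000 per arm, dropout of no more than 35%, planned GAD-7 effect d=0.13.

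- Possible loss per arm, if equal: 1000 × 0.35 = 350, leaving 1000 − 350 = 650.
- Possible loss overall: 2 × 350 = 700 of 2000.

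Follow-up effort thus acts on a large group, and the effect sought is about one eighth of a standard deviation.

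**The case against.** The best reply is that both arms are sent to online self-help resources, and the email template is not shown. Participants may not know that two services are being compared, or which one is being tested, so expectations could be similar in the two arms. This stands as far as it goes: neither the existence nor the direction of a differential bias is shown. It supports a claim of blinding to the hypothesis, if that is true, but not the claim actually made.

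Several stronger readings are tempting, and the documents do not support them:

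- *Fraud-check decisions could differ by arm.* Ethical Considerations places the check before the baseline questionnaire, and Randomization and Table 1 place allocation at week 1, after baseline. The check comes before there is an arm to know.
- *The same staff run fraud checks, reminders and follow-up with knowledge of allocation.* The article uses several terms for these staff and nowhere says they are the same people. Reminders are described without distinction by arm.
- *Only the intervention arm is monitored.* The Control section says so, but Duration and Assessments and Table 1 point the other way. This is a contradiction to resolve, not an established asymmetry.
- *Expectation bias would make up a given share of the target effect.* The article gives no size for such a bias, so any percentage would only restate an assumption.

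The statistician is described as unaffiliated with the study. That is not stated to mean blinded, and it would not blind participants in any case.

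**Conclusion.** The point holds in two parts. First, the claim that participants are blinded about the groups is wrong as written: they are sent to two recognisably different services, no masking is described, and the mechanism named cannot provide any. Second, the article contradicts itself on who sends the group-specific invitations, so blinding of the research team is not established either. The conflict over monitoring by arm adds to this.

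The size of any bias cannot be derived from the documents. It matters because the primary outcome is self-reported, the planned GAD-7 effect is only d=0.13, and up to 35% dropout is expected. The conclusion assumes that the unseen invitation template does not disguise the services, which would be hard to square with a named portal that has its own sign-on. An open comparison of two digital services is a legitimate design; the fault lies in the label and in the unreconciled procedures.

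**What to change.** 1. In the Abstract, Trial Design, Randomization and Blinding, replace the double-blind label with a statement that participants are not blinded to the tool they receive. Add, only if true, that they are not told the hypothesis. Name which staff are actually blinded.
2. In Randomization, remove the claim that simple randomization ensures blinding.
3. In Randomization, remove in-study personnel as senders. Let group-specific invitations go out only through the outside assistant, or automatically through REDCap, and do not give follow-up staff the allocation. For participants already invited, report which route was used.
4. Reconcile Blinding, Control, Duration and Assessments, Limitations and Table 1 on which arms are monitored at weeks 6 and 26.
5. In Limitations, state that self-reported outcomes are open to expectation bias and that this matters for an effect as small as d=0.13.

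Most of this is wording. Item 3 is a small procedural change in a system already in use. Because recruitment is under way, it may need an ethics amendment and can protect only invitations still to be sent. The remaining cost is a less favourable design label.

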### Intervention

The intervention group will be invited to the WTC portal, which provides options for digital interventions. A single-sign on system used by WTC will be used to facilitate ease of transfer.

### Control

The control group will be referred to the usual care tools available on the CAMH website, particularly (different mental health programs and resources such as “Game Changers: Self-care information,” which is a hub of resources to help start conversations about health, self-help booklet series, relaxation guides, and free web-based education with a personalized dashboard), which provides an opportunity to clients for self-monitoring (symptoms or physiological processes), build awareness, improve self-efficacy, and visualization. The control group will not receive process monitoring assessments at week 6 or 26. Service usage and contamination in the control group will not be monitored.

### Duration and Assessments

The expected duration of each participant’s involvement in the study is for 6 months with baseline, weekly short follow-ups, intervention monitoring, and final assessments. Participants from the intervention and control groups will be asked to fill 1 baseline assessment at week 0 and 12 biweekly follow-ups from week 2 until week 24 including process monitoring of the intervention at weeks 6 and 26. Lastly, one final assessment will be carried out at week 26, for a total duration of 6 months. Hence, in total, a participant will complete 14 assessments. Participants will be sent weekly reminder emails to complete the assessments for compliance. The study team will track people who are lost to follow-up by communicating with them regularly through weekly emails and will continue to do so until the end of the study. They will be sent emails every week and will be provided an opportunity to complete the assessments when they show up until the end.

### Ethical Considerations

This study is approved by the Research Ethics Board (REB) of CAMH (reference <REB#: 037-2022>, version 7.0). The protocol will be reapproved by the REB if it requires amendment. Participants will be screened and provided a unique ID number to protect their personal information. An electronic informed consent form has been prepared in REDCap to remotely obtain consent from the participants prior to enrolling them in the trial. A REDCap survey has also been designed separately for participants’ eligibility screening at baseline, biweekly follow-ups, intervention monitoring, and final assessment over the 26-week period. Participants will be allowed to withdraw at any time without penalty.

Participants who meet the eligibility requirements of the initial screening form will be prompted to fill out a contact form with their first name and email address. Participants deemed eligible after a manual fraud check will be emailed a personalized URL to the baseline questionnaire by the research staff and those who are deemed ineligible by the fraud check will be sent a notification from REDCap about their ineligibility. The baseline questionnaire is largely composed of questions about age, sex, gender, race and ethnicity, education, and 3 digits of the participants’ postal code to later connect it with census data and community-level equity data. Lifetime history of substance use and mental health will be ascertained, including problematic alcohol use (assessed using Alcohol Use Disorders Identification Test item 3 about how often they had 6 or more drinks on 1 occasion in the past year) and drug use (assessed using the modified Drug Use Disorders Identification Test). Finally, we will measure time to completion for data quality reasons, but this variable will not be visible to participants.

This randomized population trial will be compensating thousands of participants (N=2000). We will compensate participants at a rate sufficient to motivate them to comply with the study protocol and to complete all surveys and measures. This will include a CAD $10 (US $7.24) Giftbit [19] e-card after completing the initial baseline survey at week 0, and then CAD $24 (US $17.38) for completing the 12 assessments during biweekly follow-up in weeks 2-24, and finally CAD $10 (US $7.24) for final assessments at week 26. The follow-up payment will be based on completion rate, which, in turn, is based on the number of assessments completed at a rate of CAD $2 (US $1.45) biweekly. Hence, a participant completing 100% of the assessments (N=14) will receive CAD $44 (US $31.87) in total.

### Privacy and Confidentiality

The master linking log will be stored in a separate folder than the other data files on the CAMH server. The master linking log will be used to identify contact information in order to send the baseline questionnaire link, follow-up questionnaire, and gift cards; to store status of interest in the qualitative study and future research studies; and to monitor completion of baseline and follow-up surveys. A numerical participant ID number will be used to differentiate participants in an anonymous manner across measures and follow-up questionnaires. 

Participants who complete surveys will receive e-gift cards through Giftbit, which allows one to select a gift card of one’s choice. Giftbit Incentives is a secure platform that allows bulk and automated sending of e-gift cards, and has been used by the principal investigator (MC) in previous studies at CAMH. Participant information shared with Giftbit will be limited to their first name and email address, in order to allow personalized e-gift card emails. 

### Safety and Adverse Events

Since the study procedures are not at higher than minimal risk, adverse events (AEs) and serious AEs (SAEs) are not expected. If any unanticipated problems related to the research involving risks to participants or others occur during this study, they will be reported to applicable stakeholders in alignment with institutional policies. AEs that are not serious but are notable and could involve risks to participants will be documented in accordance with institutional documentation requirements.

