### Participant Withdrawal Criteria

Participants will not be withdrawn from the study for not wanting to receive the WTC or control intervention. Participants’ intention to use and the reason to not use the intervention will be identified through self-assessments. However, they will be withdrawn from the study if suicidal thoughts occur in any of the long-term follow-up assessments at weeks 4, 8, 12, 16, 20, and 24.

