#### Secondary Outcomes

An economic analysis will be conducted by comparing incremental costs and health outcomes for the Wellbeing Tracker and WTC compared to within-person expected trajectories using a cost-effectiveness acceptability curve. These costs will be based on the costs associated with the ongoing recruitment and maintenance costs of WTC compared to the cost per QALY gained through the use of these interventions [20]. To be somewhat comparable with World Health Organization’s standards for ranking public health interventions, the determination of whether the WTC overall is highly cost-effective will be based on a threshold of CAD $124 (~US $100) per QALY gained [21]. QALYs will be estimated using the SF-6D (Short-Form Six-Dimension), calculated on the basis of the SF-12 (12-item Short Form Survey) [21]. This analysis will provide an empirical basis for the effect of allocation of health care resources in Canada. To aid other countries, we will also base cost-effectiveness calculations based on estimations that incorporate implementation costs of the Wellbeing Tracker and WTC. We will also estimate cost-effectiveness based on clinically Reliable Change Index scores (ie, 5 points on the PHQ-9 [22] and a 6-point change on the GAD-7 [23], as well as employment status. The schedule of the Let’s Act on Mental Health study is outlined in Table 1.

**Table 1 table1:** Schedule of the Let’s Act on Mental Health Survey of 2022.

Procedures	Study period (day 1 to week 26)						
Enrollment	Day 1	Week 0	Week 1	Weeks 2 and 4	Week 6	Weeks 8-24	Week 26
Eligibility screening	✓						
Informed consent	✓						
Screening assessments (PHQ-9^a^ item 9)	✓						
Drug use (DUDIT-C modified^b^)	✓						✓
Problematic alcohol use (AUDIT-C^c^)	✓						✓
Enrollment							
Demographics		✓					
3-Digit postal codes		✓					
Baseline with self-reported questionnaires (GAD-7^d^, PHQ-4^e^, Current Substance Use, SF-12^f^, and WSAS^g^)		✓					
Randomization to the WTC^h^ intervention or usual care group through an email invitation			✓				
Biweekly short and long follow-up (GAD-7, PHQ-4, Current Substance Use, SF-12, and WSAS)				✓		✓	
WTC and usual care monitoring for contamination and compliance checks					✓		✓
Final assessment (GAD-7, PHQ-4, current substance use, SF-12, and WSAS)							✓

^a^PHQ-9: 9-item Patient Health Questionnaire.

^b^DUDIT-C modified: modified Drug Use Disorders Identification Test.

^c^AUDIT-C: Alcohol Use Disorders Identification Test.

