## Discussion

### Anticipated Findings

At baseline, with regard to gender and race, a greater proportion of participants are female (n=359, 75.57%) and White (n=335, 67.95%). We aim to generalize this study to the Canadian population; hence, we have been weighting samples at the census level based on gender and province to make this study representative. Weighing of the sample will help us understand how generalizable the sample and advertisements are and whether they are adequately representative. The SF-12, measuring mental and physical health, has revealed a significant decline in mental health from baseline to short and long follow-ups in this study. It is too early to discuss how this will develop longitudinally, but the preliminary results suggest a larger decline in mental health than in physical health in the Canadian population.

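### The adverse-event rule leaves foreseen or unrelated serious events uncovered, and the harm wording under Blinding has no individual-level harm outcome behind it

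*Protocol article*

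**What the plan says.** All references are to the protocol article.

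- **Safety and Adverse Events** opens with the expectation "Since the study procedures are not at higher than minimal risk, adverse events (AEs) and serious AEs (SAEs) are not expected". Two rules follow. The first covers reporting: "If any unanticipated problems related to the research involving risks to participants or others occur during this study, they will be reported to applicable stakeholders". The second covers documentation: "AEs that are not serious but are notable and could involve risks to participants will be documented in accordance with institutional documentation requirements". Both defer to institutional requirements.
- **Exclusion Criteria** (and Textbox 1) bar people at risk for suicide, judged from the PHQ-9.
- **Participant Withdrawal Criteria** says of participants in follow-up that "they will be withdrawn from the study if suicidal thoughts occur in any of the long-term follow-up assessments", and names weeks 4, 8, 12, 16, 20 and 24.
- **Blinding** says the results will be used to assess the portal's effectiveness, "which is the extent to which the service benefits the patients rather than doing them any harm".
- **Primary Outcomes** and **Statistical Analysis** plan a comparison of anxiety and depression trajectories with control by random-effects and multilevel models, with demographic interactions, under intention to treat.
- **Secondary Outcomes** holds the only individual-level change criteria, 5 points on the PHQ-9 and "a 6-point change on the GAD-7", and uses them for cost-effectiveness.
- **Table 1** ticks PHQ-9 item 9 on day 1 only. Its follow-up and final rows list GAD-7, PHQ-4, substance use, SF-12 and WSAS.

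**The concern.** The safety section builds its rules on the expectation that no AEs will occur, while two other sections treat suicidality as foreseeable. An outcome with six scheduled checks is not unanticipated. The reporting rule therefore does not reach it, and the documentation rule is confined to non-serious events.

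The article also tells its readers that the trial informs on harm, yet it names no outcome that counts participants who got worse. Two things are at stake. A foreseen serious event could go unrecorded as an AE without any breach of the text. A favourable average trajectory could also be read as absence of harm when nobody has counted deterioration by arm.

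**Working it through.** **1. Which events do the two safety rules cover?** The reporting rule requires an event to be both unanticipated and research-related. The documentation rule requires it to be non-serious and notable, and sets no condition on expectedness or relatedness.

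| Event | Reporting rule | Documentation rule |
|---|---|---|
| Unanticipated and related, serious | yes | no |
| Notable, non-serious, foreseen or not, related or not | only if unanticipated and related | yes |
| Serious and foreseen | no | no |
| Serious, unanticipated, judged unrelated | no | no |

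Suicidal thoughts in follow-up are foreseen, because the withdrawal rule names them. If graded non-serious and notable, they are documented. If graded serious, they fall in the third row and neither rule applies. The article does not say which grading is used.

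**2. Which measure yields suicidal-thought events?** The withdrawal rule needs one at weeks 4 to 24. Table 1 lists PHQ-9 item 9 on day 1 only and the PHQ-4, not the PHQ-9, afterwards. On that schedule no listed item is identified as the source. The withdrawal rule and Table 1 must be reconciled before such events can be counted.

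**3. What can the stated analyses show?** The trajectory comparison is two-sided in effect and can detect average worsening. Inputs: 1000 per arm and 35% dropout (Sample Size), giving 1000 × (1 − 0.35) = 650 per arm, two-sided 5%. The smallest detectable standardised difference is (z₀.₉₇₅ + z_power) × √(2/n):

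- 80% power: (1.960 + 0.842) × √(2/650) = 0.155
- 90% power: (1.960 + 1.282) × √(2/650) = 0.180

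This is a simple two-group calculation that ignores any gain from repeated measures. The demographic interactions give averages within subgroups. Neither analysis counts individuals who deteriorate.

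**4. How far can an average hide individual worsening?** This is an illustration. The 5% is invented, and the GAD-7 SD of 4 to 5 is assumed because the article gives none.

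- Extra deterioration in one arm: 0.05 × 1000 = 50 people, each by 6 points, the article's own threshold.
- Shift in the arm mean: 0.05 × 6 = 0.30 points.
- In SD units: 0.30/5 = 0.06 to 0.30/4 = 0.075, at most about half of the 0.155 found in step 3.
- Planned GAD-7 effect d = 0.13: 0.13 × 4 = 0.52 to 0.13 × 5 = 0.65 points.
- If that benefit applied before the extra deterioration, the net would be 0.52 − 0.30 = 0.22 to 0.65 − 0.30 = 0.35 points, still favourable.

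**5. Does withdrawal affect the averages?** The article does not say whether withdrawal for suicidal thoughts ends assessment. If it does, some of the worst courses leave the trajectories, while Statistical Analysis assumes that data are missing at random. The average comparison would then be a weaker guard against harm than step 3 suggests.

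**The case against.** The strongest reply has four parts.

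*The safety section does provide for events that occur.* This stands. A reader might infer that only unanticipated, related problems are captured, or that AEs have been defined away. The last sentence of the section rules that out for notable non-serious events. Likewise, saying that AEs are not expected refers to the study procedures and is weaker than assuming no harm. The gap is confined to serious events that are foreseen or judged unrelated.

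*This is a condensed article that defers to institutional policy.* This stands for AE collection, grading and tabulation in general, whose absence here is no finding. It does not remove the conflict between what the article itself states: its reporting trigger, its expectation of no AEs, and its scheduled response to suicidal thoughts.

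*Harm can be assessed, and the Blinding sentence only explains effectiveness.* Largely right. A reader might infer that no statement on harm could ever be drawn, but the randomised trajectory comparison can show average worsening. The sentence also announces no safety conclusion. It does mention harm, however, and the stated analyses cannot support that for individual deterioration or suicidality.

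*The early decline proves nothing.* Right. Anticipated Findings reports that the SF-12 "has revealed a significant decline in mental health from baseline to short and long follow-ups in this study". It is tempting to read this as a sign of harm from the portal. It is preliminary and not given by arm, so it is no such evidence. It shows only that worsening during follow-up is foreseeable in this sample.

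**Conclusion.** The point holds in a limited form. As written, a serious event that is foreseen or judged unrelated is covered by neither safety rule, although the article itself foresees suicidal thoughts at six visits. The reference to harm under Blinding rests on between-arm averages alone.

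The size of any missed harm cannot be estimated from the document. The 50-person scenario shows only that a mean shift of 0.30 points can sit inside a planned benefit of 0.52 to 0.65 points. It is not a forecast, and it depends on the assumed SD and the invented 5%.

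The conclusion rests on a literal reading of the safety section. The institutional policies, which are not shown, may close the gap in practice. Even so, the wording should be corrected, because the article's own passages disagree.

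**What to change.** 1. Reconcile Safety and Adverse Events with Exclusion Criteria and Participant Withdrawal Criteria, so that foreseen events are recorded in both arms whatever their expectedness or judged relatedness.
2. Reconcile Participant Withdrawal Criteria with Table 1, so that it is clear which measure yields suicidal-thought events and when. Until this is done, those events cannot be counted reliably.
3. Have the unaffiliated statistician named in Statistical Analysis tabulate two outcomes by randomised arm, each with the difference and its confidence interval. The first is reliable worsening, defined as a GAD-7 increase of at least 6 points from week 0 (the Secondary Outcomes threshold). The second is withdrawal for suicidal thoughts. Fix the time point for the first in advance, and show the number assessed in each arm beside each count. Production by this statistician lets the study team remain blinded.
4. Limit the harm wording under Blinding to these outcomes and to average worsening.

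The cost is some rewording and one extra table. GAD-7 is already collected in both arms, so the first outcome needs no new data. The second depends on item 2. The small downside is that the trial will report non-zero harm counts in both arms.
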